#### Analysis of the randomized controlled trial

Our primary analysis will be an intent-to-treat (ITT) causal effect estimation of our registered pre-specified primary and secondary outcomes. The effect sizes determined in the primary analysis provide an unbiased measure of the real-life policy impact of our intervention. As a secondary analysis, we will also conduct a contamination-adjusted intention-to-treat analysis (CA ITT) using an instrumental variable to adjust for bias [58]. For the CA ITT analysis, we will use the random assignment to intervention vs. control facility catchment area of this trial as an instrumental variable (IV) to measure the effect size that would have been attained without “contamination.” Contamination occurs when women who live in an intervention area do not utilize the MMHW and women who live in a control area utilize the MMHW to receive health care. The treatment in the IV analysis is participants’ actual MMHW registration status. The effect size determined in this secondary analysis provides a measure of the full effect that the intervention would have induced in the absence of intervention utilization (or lack thereof) that did not conform with the intervention status intended by the random assignment of geographical communities. We will regress the primary and secondary outcomes (Table 1) on the random assignment of participants to facility catchment intervention vs. control area. For our binary outcomes, we will use modified Poisson regression analysis [59]; for our count outcomes, we will use negative binomial regression; and for our continuous outcomes, we will use linear regression for effect size estimation.

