Cost per additional ANC visit^a^	Cost-effectiveness ratio: effect on the second primary outcome divided by effect on the third primary outcome	Ratio	Quantitative household survey, MMHW dashboard
Financial distress^a^	Woman reporting at least one sign of financial distress	Binary variable	Quantitative household survey
Time to seek medical attention^a^	Time from first symptoms until professional medical care was accessed	Continuous time variable	Quantitative household survey
MMHW usage^a^	Woman who used the MMHW to pay for ANC or delivery-related expenses either in part or entirely	Binary variable	Quantitative household survey
Patient satisfaction^a^	Patient satisfaction with health facility and MMHW	Likert scale, qualitative interviews	Quantitative and qualitative household survey
Health system satisfaction^a^	Satisfaction with the health system	Likert scale, qualitative interviews	Quantitative and qualitative household survey
Life satisfaction	Satisfaction with general life situation	Likert scale, qualitative interviews	Quantitative and qualitative household survey
Time of sign-up	Time of sign-up to MMHW in relation to delivery date	Continuous time variable	Quantitative household survey, MMHW dashboard

^a^Pre-registered outcomes at DRKS (Deutsches Register Klinischer Studien, German Clinical Trials Register, identifier: DRKS00014928); *MMHW* maternal mobile health wallet, *ANC* antenatal care, *C-section* caesarean section

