#### Community and home-based procedures

Within both the intervention and control groups of the trial, CHWs will fulfill two functions as part of their routine maternal health activities: (i) to identify pregnant women at the community level during household visits and refer them for ANC or delivery to the nearest primary-care health facility and (ii) to inform pregnant women and their relatives during household visits or community dialogues about general health issues (such as nutrition, immunization, hygiene) and the importance of seeking skilled care during delivery or in case of illness during pregnancy. In the intervention group, CHWs will assume the additional task of informing pregnant women about the MMHW and will encourage them to register for the service. To this end, CHWs will receive information material and training and their feedback will be collected regularly by members of the trial staff. For each user that they sign-up to the MMHW and for each active user of the MMHW, CHWs will receive a small performance-related bonus via MM. However, CHWs in Madagascar’s public health system are involved in a multitude of public health activities and, depending on the type and timing of other interventions, may be unavailable at times for MMHW-related tasks [51]. Thus, in addition to CHWs, dedicated midwives will be employed exclusively for MMHW-related activities to ensure continuous sensitization of pregnant women and relevant stakeholders and to obtain support for the intervention from community leaders. Dedicated health workers will also actively follow up with MMHW users through household visits and phone calls to ensure that they have taken up ANC and to support first and future savings in preparation of delivery through information, education, and counseling. In addition, a toll-free, three-digit hotline providing information and support around MMHW-relevant topics is available to the general public, users, and health facilities.

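### The contamination-adjusted analysis defines contamination and its target by use of the MMHW but codes treatment as registration, so it estimates the effect of registering, not the effect it describes

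*Protocol article*

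**What the plan says.** All of this is in the Protocol article. The section Analysis of the randomized controlled trial makes intention-to-treat (ITT) the primary analysis and adds the CA ITT as a secondary one, with random assignment of the catchment area as the instrument. Three consecutive sentences or statements then matter.

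- Definition: "Contamination occurs when women who live in an intervention area do not utilize the MMHW and women who live in a control area utilize the" wallet to obtain care.
- Treatment variable, in the next explicit specification: "The treatment in the IV analysis is participants’ actual MMHW registration status".
- Target: the result is said to measure "the full effect that the intervention would have induced in the absence of intervention utilization (or lack thereof) that did not conform" to the assigned status.

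Registration and use appear as separate items elsewhere. Table 1 defines the outcome MMHW usage as "Woman who used the MMHW to pay for ANC or delivery-related expenses either in part or entirely", and lists time of sign-up on its own row as "Time of sign-up to MMHW in relation to delivery date". The section Community and home-based procedures pays community health workers on both counts: "For each user that they sign-up to the MMHW and for each active user of the MMHW, CHWs will receive a small performance-related bonus". The Discussion relies on the CA ITT as its answer to contamination bias.

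**The concern.** The definition and the target are framed by use, while the variable that goes into the model is framed by registration. For any woman who registers and never uses the wallet, the two rules disagree. In an intervention area she is contaminated under the definition and treated in the model. In a control area a woman who registers without using is coded as treated although the definition does not count her as contaminated.

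An instrumental-variable (IV) estimate scales the ITT effect by the between-arm difference in the treatment variable. The choice between registration and use therefore decides both the number reported and what it means. Followed as written, the plan would report an effect of registering under a description that speaks of utilisation. Because both the definition and the treatment variable are already fixed in this text, the conflict is not a detail left open for an analysis plan to fill in.

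**Working it through.** The article gives no figure for the CA ITT, so there is none to reproduce. The check has three parts.

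**1. How each group is classified**

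| Woman | Contaminated under the stated definition? | Coded as treated in the IV? |
|---|---|---|
| Intervention area, registered, used | No | Yes |
| Intervention area, registered, never used | Yes | Yes |
| Intervention area, not registered | Yes | No |
| Control area, registered, used | Yes | Yes |
| Control area, registered, never used | No | Yes |
| Control area, not registered | No | No |

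The definition and the coding conflict in the second and fifth rows. They agree throughout only if every registrant uses the wallet.

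**2. How far apart the two ratios can be**

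Inputs from the Power calculation section: an ITT difference of 4 percentage points in facility delivery, used purely as an illustration, and 50% adoption in intervention areas. Assumptions not in the document: adoption is read as registration, nobody in control areas registers, and a share *c* of registrants use the wallet. The ratio is taken on the risk-difference scale.

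- Registration-coded ratio = ITT / (difference in registration) = 4 / 0.50 = 8.0 points.
- Use-coded ratio = ITT / (difference in use) = 4 / (0.50 × *c*).

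| Assumed *c* | Use-coded ratio (points) | Relative to 8.0 |
|---|---|---|
| 100% | 8.0 | 1.00 |
| 90% | 8.9 | 1.11 |
| 75% | 10.7 | 1.33 |
| 50% | 16.0 | 2.00 |
| 25% | 32.0 | 4.00 |

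The factor is 1/*c* whenever *c* is equal in both areas. With 5% registration in control areas and *c* = 75%, the ratios are 4 / 0.45 = 8.9 and 4 / (0.45 × 0.75) = 11.9, again a factor of 1.33.

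The range depends on what adoption means. If the 50% is use, registration is 0.50 / *c*. At *c* = 80% that is 62.5% registered, and the ratios are 4 / 0.625 = 6.4 and 4 / 0.50 = 8.0. At *c* = 50% everyone is registered, and the ratios are 4.0 and 8.0. A lower *c* is impossible, so under that reading the factor cannot exceed 2.

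**3. Whether the use-coded ratio would be the right answer**

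Take 50% registered in intervention areas, none in control areas, half of registrants using, and an assumed 12-point effect in users.

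- If registering without use does nothing: ITT = 0.50 × (0.5 × 12 + 0.5 × 0) = 3 points. The use-coded ratio is 3 / 0.25 = 12, which is the effect in users. The registration-coded ratio is 3 / 0.50 = 6, the average effect over registrants.
- If registering without use gives 4 points, for example through vouchers or follow-up: ITT = 0.50 × (0.5 × 12 + 0.5 × 4) = 4 points. The use-coded ratio is 4 / 0.25 = 16, which overstates the 12 points in users. The registration-coded ratio is 4 / 0.50 = 8, still the average over registrants.

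In both cases the registration-coded ratio is what it ought to be: the effect of registering among women who register because of assignment. The use-coded ratio is right only if registration without use has no effect.

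**The case against.** The strongest reply is that registration is simply the operational measure of use. The sentence naming it directly follows the definition of contamination. The article often calls registrants users, and using the wallet to receive care could include redeeming a voucher without any wallet payment. The Table 1 usage outcome is a narrower payment measure that the analysis section does not cite. This has some force: the payment definition should not be read into the contamination sentence as if it were stated there. It does not remove the conflict, because a woman who registers and then neither redeems nor pays has not used the wallet on any reading. The article also separates sign-ups from active users in its bonus scheme.

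Three stronger readings are tempting, and the document supports none of them.

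- A reader might infer that the planned estimate is too small by the factors tabulated above. Those factors rest on assumed conversion shares. They measure the distance to an estimator whose exclusion assumption is doubtful here, since vouchers follow sign-up once the account is validated, and dedicated workers visit and call registered women.
- A reader might infer that many registrants never use the wallet. The Background does mention withdrawn services, but these are other services, and low demand is given as an alternative reason. In this trial, bonuses for active users and support for first savings encourage use.
- A reader might infer that the trial's main result is affected. The CA ITT is labelled secondary and the ITT does not involve the treatment variable.

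**Conclusion.** The concern holds as a mismatch between a stated target and a specified analysis. Whenever some registrants never use the wallet, the CA ITT does not deliver the effect without non-conforming utilisation. Under the usual instrumental-variable assumptions it delivers the effect of registration among women whose registration follows assignment.

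The size of the gap cannot be determined from the document. It is a factor of 1/*c* if the share *c* of registrants who use the wallet is equal in both areas, and nil only if *c* is 100%. The choice of registration as the treatment is defensible; what is wrong is the description around it. Facility-level training and equipment could affect outcomes outside either coding, but that is a separate matter. The consequence is confined to how one secondary analysis is labelled and interpreted, which matters because the Discussion leans on it to deal with contamination.

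**What to change.** In Analysis of the randomized controlled trial:

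1. Keep registration status as the treatment in the IV analysis.
2. Redefine contamination as not registering in an intervention area, or registering in a control area.
3. Replace the utilisation-based description of the full effect with the effect among women who register because of assignment.
4. Report by arm the share of registered women who used the wallet.
5. Give the ratio based on the Table 1 MMHW usage variable only as a labelled sensitivity analysis. State that it assumes registration has no effect on outcomes other than through use.

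The cost is a few sentences, one extra ratio and a narrower stated conclusion. No new data are needed: usage is already a survey outcome and registration is already the planned treatment variable. By the Trial status section, outcome assessment starts on January 1, 2022, so on the article's own timeline the change can precede it.

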### Procedures

#### Intervention package

The intervention package examined in this study consists of three elements: (i) the MMHW for restricted health savings during pregnancy, (ii) conditional cash transfers and electronic vouchers for maternal and neonatal healthcare services and emergency evacuation, and (iii) quality of care assessments and trainings for facility-based health workers. The intervention package is implemented by a non-governmental organization in partnership with the Malagasy Ministry of Health’s UHC program. Sequential implementation of the intervention package commenced in January 2019 and all randomized facilities received the intervention at least since May 2020.

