#### Health facility-based procedures

Health facilities within the intervention group of this study will receive a smart device such as a phone or tablet with mobile internet access and running the MMHW web-based interface and facility-based health workers will be trained in its use. In addition, health workers will also receive training on general aspects of the MMHW enabling them to provide information about the intervention to eligible patients and to collect user feedback. Health facilities within the intervention group will also be invited to take part in a quality assurance program consisting of an annual structured quality assessment followed by a 3-day refresher training for facility-based health workers on routine maternal and newborn care and on complications during pregnancy and childbirth. The quality assessment and refresher training will be performed by representatives of the Ministry of Health. Furthermore, health facilities in the intervention group are entitled to receive small donations of medical equipment including stethoscopes, blood pressure cuffs, weight scales, and sharps disposal containers if deemed necessary by the quality assessment.

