The 4MOTHERS trial has several limitations. First, the catchment areas of participating public-sector health facilities selected for the population-based survey are randomly distributed throughout the study region. This creates many boundary areas between intervention and control facilities, which can lead to possible contamination bias should women who live in the catchment area of a control health facility inadvertently be exposed to the intervention, thus potentially minimizing the difference in outcomes between the two groups. Thus, to adjust for contamination bias, we will conduct a CA ITT analysis. Second, the trial takes place in a real-life setting where normal service delivery and targets have to be ensured by participating health facilities alongside the trial intervention, which might impact the adoption of the intervention by health workers. Third, the particular design of the MMHW may impact the uptake and efficiency of the intervention. The trial thus has to be considered as a test of the MMHW “in real life,” and we cannot necessarily conclude from a null finding that mobile money-based savings and payment service for maternal healthcare cannot be effective in another context. Fourth, women who receive the intervention will be entitled to conditional cash transfers and electronic vouchers for free ANC drugs, prenatal ultrasound exams, and emergency evacuation to a reference hospital, which may have an independent effect on maternal and neonatal health outcomes. Therefore, the results of the study can only be considered for the intervention as a whole and should not be reduced to MMHW alone. However, they should be interpreted in the context of effective delivery of conditional cash transfer and electronic vouchers as an inherent strength of the MMHW.

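### The contamination-adjusted analysis treats MMHW registration as the only route to the outcomes, so its full-effect interpretation is not supported

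*Protocol article*

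**What the plan says.** In the protocol article, *Analysis of the randomized controlled trial* makes ITT the primary analysis. It adds a contamination-adjusted ITT (CA ITT) as a secondary analysis, with random assignment of the catchment area as the instrument. The exposure is fixed: "The treatment in the IV analysis is participants’ actual MMHW registration status". So is the interpretation: "The effect size determined in this secondary analysis provides a measure of the full effect that the intervention would have induced", had no woman's use departed from her assigned arm.

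The same section defines contamination by use rather than registration: "Contamination occurs when women who live in an intervention area do not utilize the MMHW", or when women in control areas do use it. Table 1 lists MMHW usage (paying through the wallet) as an outcome of its own.

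Other sections describe what assignment brings:

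- *Intervention package*: the third element is "quality of care assessments and trainings for facility-based health workers".
- *Health facility-based procedures*: a three-day refresher course for staff, and "health facilities in the intervention group are entitled to receive small donations of medical equipment" where the assessment finds a need.
- *Community and home-based procedures*: dedicated midwives who sensitize pregnant women and seek community leaders' support.
- *Control group*: no such assessments or training beyond routine Ministry activity.

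The Discussion offers the CA ITT as the answer to contamination bias. It also says that "the results of the study can only be considered for the intervention as a whole and should not be reduced to MMHW alone".

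**The concern.** Assignment is a valid instrument for registration only if it changes outcomes through registration and by no other route (the exclusion restriction). A better trained or equipped facility can change the care, and the care-seeking, of a woman who never registers. The instrumental-variable (IV) estimator divides the whole ITT difference by the difference in registration, so anything gained or lost by non-registrants is credited to registrants.

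This matters because the Discussion presents the CA ITT as the correction for contamination. Readers will tend to take it as the undiluted answer. As specified, it may replace dilution with a bias of unknown size, under a sentence that claims more than the design can deliver.

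**Working it through.** **1. Which elements run through registration?**

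- Savings bonus and vouchers: tied to wallet use or sign-up (*Restricted cash transfers and electronic vouchers*). No breach of the exclusion restriction.
- Follow-up visits and calls by dedicated health workers: directed at MMHW users. Largely through registration.
- The extra task of community health workers: to inform women about the wallet and encourage sign-up. Largely through registration, although the contact may have effects of its own.
- Sensitization of pregnant women and community leaders by dedicated midwives: can reach women who do not register. A partial bypass.
- Quality assessments, refresher training and equipment: act at facility level, whoever is registered. A bypass.

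The article neither states nor defends the exclusion restriction.

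**2. Size of the bias.** The documents give no figure for the IV analysis, so there is none to reproduce. The inputs are:

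- Uptake p = 0.50 (*Power calculation*). I take adoption there to mean registration.
- Control-arm registration: not given. Assumed 0, with a range to 10%.
- Effects a (registrants in intervention areas) and b (non-registrants there): not given. They are on the difference scale.

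Then

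ITT = p·a + (1−p)·b

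IV = ITT / p = a + b(1−p)/p

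- p = 0.5: (1−p)/p = 1, so the bias is b.
- p = 0.3 (assumed): 0.7/0.3, so the bias is 2.33b.
- p = 0.7 (assumed): 0.3/0.7, so the bias is 0.43b.

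An extreme case shows the mechanism. If registering adds nothing and the rest of the package gives every woman 2 points (a = b = 2), ITT = 0.5×2 + 0.5×2 = 2, and IV = 2/0.5 = 4 points.

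**3. Illustration with the protocol's 4-point difference.** *Power calculation* names a 4-point increase in facility delivery. I use it only as a convenient ITT value; whether the trial has the stated power to detect it is a separate question. At p = 0.5 the IV estimate is 4/0.5 = 8.0 points whatever b is, while a = (4 − 0.5b)/0.5:

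| Assumed b (points) | a (points) | IV estimate | IV minus a |
|---|---|---|---|
| −1 | 9.0 | 8.0 | −1.0 |
| 0 | 8.0 | 8.0 | 0 |
| 0.4 | 7.6 | 8.0 | 0.4 |
| 1 | 7.0 | 8.0 | 1.0 |
| 2 | 6.0 | 8.0 | 2.0 |

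Here a is the total effect on a registrant. If the bypass elements also give registrants b, the part due to registration is a − b. For b = 1 that is 6.0 points, against an IV estimate of 8.0. A simulation with 2 million women agreed: for b = 1 it gave 8.1, for b = 2 it gave 7.9, and for b = −1 it gave 7.9.

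**4. Control-arm registration above zero.** Let p1 and p0 be registration in the two arms, with additive effects and b reaching all women in intervention areas. The bias against a is then b[1/(p1−p0) − 1]. With p1 = 0.50:

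- p0 = 0.05: 1/0.45 − 1 = 1.22, so the bias is 1.22b.
- p0 = 0.10: 1/0.40 − 1 = 1.50, so the bias is 1.50b.

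**5. Who the estimate describes.** Even with b = 0, the IV estimate applies to compliers: women who register if their area is assigned the intervention and not otherwise. At 50% uptake that is about half the women. The full-effect sentence extends it to the rest, which needs equal effects in both groups. The article does not state that assumption.

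**The case against.** The strongest counter-case has four parts.

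- **Nothing shows that the restriction is broken in practice.** A reader might infer that the exclusion restriction demonstrably fails and that the CA ITT overstates the effect. The documents do not support that: they give neither size nor sign for effects on non-registrants. Facilities are invited to join the quality programme, equipment depends on need, and many women do not deliver at these facilities (the region's 68% facility-delivery figure includes private ones). A negative b would give an understatement. For total healthcare expenditure the direction is open. This objection stands, and it limits the claim to a restriction that is not credible as described.
- **Much of the outreach is the first stage.** It works by getting women registered. This stands too; only the facility elements and some sensitization count as bypass routes.
- **The Discussion already warns against reducing results to the wallet.** It does, but the warning is about cash transfers and vouchers, which run through the wallet. It does not mention the facility elements or qualify the IV analysis.
- **IV assumptions and sensitivity analyses belong in the SAP.** Often so, and their absence alone would be no finding. Here the article itself fixes both the treatment variable and the interpretation.

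On registration against utilization, registration is arguably the less vulnerable choice, because vouchers are issued at sign-up. What remains is a mismatch of definitions to be reconciled.

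**Conclusion.** The point holds in a conditional form. The protocol's own account of the package gives assignment routes to the outcomes that bypass registration, so the exclusion restriction is not credible and the full-effect interpretation is unsupported. At 50% uptake with no control-arm registration, the bias equals the effect b on non-registrants. It is larger at lower uptake or with control-arm registration. It is upward if b shares the sign of the effect, which is plausible for facility delivery and antenatal visits because improved access is the trial's hypothesis. The values of b used here are assumptions. Separately, a valid instrument would still describe compliers only. The CA ITT is secondary and the primary ITT is unaffected, so this should be corrected but does not threaten the main result.

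**What to change.** Keep the ITT as primary and keep registration as the IV treatment, then:

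- Present the CA ITT as a scaled ITT that equals a complier-average effect only if assignment acts through registration alone. State that assumption and name the facility-level and sensitization elements that put it in doubt.
- Delete the full-effect sentence.
- Add a sensitivity analysis over a range of b, positive and negative, using observed registration in both arms. On the difference scale with additive effects: a = ITT/(p1−p0) − b[1/(p1−p0) − 1].
- Reconcile the definition of contamination (utilization) with the treatment (registration).

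Do not widen the treatment to include antenatal care or delivery at an intervention facility. Antenatal visits and facility delivery are primary outcomes, so a woman would count as treated because she had the outcome.

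The cost is a change of text, a little more analysis and a less definitive secondary estimate. No new data are needed, since the planned analysis already requires registration status in both arms. On the article's timeline, outcome assessment starts on January 1, 2022, so the change can precede the data.

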#### Restricted cash transfers and electronic vouchers

To incentivize users to save for perinatal medical expenses, each amount credited to the MMHW is topped up with a bonus of 50% of the saved amount. This bonus can only be used to pay for maternal healthcare services; it is not credited to a user’s MM account upon completion of the pregnancy or if a participant chooses to end MMHW membership. In addition, upon sign-up and corresponding to current WHO recommendations, users receive electronic vouchers for free-of-charge (i) ANC drugs such as iron and folic acid supplements; (ii) at least one prenatal ultrasound exam taking place before the 20th week of pregnancy and subsequent follow-up ultrasound exams if medically indicated; and (iii) emergency treatment and referral from a primary-care health facility to a reference hospital in case of a medical emergency during pregnancy or childbirth. Users are informed about their eligibility for conditional cash transfers and electronic vouchers by health workers and automated SMS messages. Users can redeem vouchers for ANC drugs at pharmacies of participating health facilities; ultrasound exams are performed by midwives specialized in prenatal ultrasound at participating health facilities at least once a month, and emergency services can be requested 24/7 by health workers using a Toll-free number. Once a new user has registered for the MMHW and before being eligible to receive restricted cash transfers or electronic vouchers, the account is validated by a facility-based health worker or dedicated MMHW health worker by uploading a photo of the user’s ID card or proof of residence using the MMHW’s web-based interface.

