### Analysis

#### Power calculation

For our baseline power calculation, we assumed a facility-based delivery rate of 67% and an average count of two ANC visits during pregnancy without the intervention [35]. The potential study population was approximately 10,000 pregnant women in the study region during the intervention period. We assumed that 50% of participants living in catchment areas of health facilities that received the intervention would adopt the MMHW. We calculated the minimum detectable difference between the intervention and control groups for the three primary outcomes using methods for cluster randomized trials. We assumed a 20% loss to follow-up and an intra-cluster correlation of 0.05. The intra-cluster coefficient (ICC) was conservative compared to ICCs that were empirically measured in similar settings [57]. Using the standard method for power calculations for binary outcomes, with a 95% two-sided confidence level, we would have 80% power to detect a 4-percentage point increase in the rate of facility-based deliveries, an 80% power to detect an increase of 0.08 average ANC visits per woman, and an increase of total health expenditure of 1700 Malagasy Ariary if we enrolled 2300 participants per group.

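### The contamination-adjusted analysis is described as giving the effect under full conformity to assignment, but it identifies only the effect in women whose registration follows assignment

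*Protocol article*

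**What the plan says.** All of this is in the protocol article.

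- **Analysis of the randomized controlled trial.** The primary analysis is intention-to-treat. A secondary contamination-adjusted analysis uses assignment of the facility catchment area as an instrumental variable. On the exposure: "The treatment in the IV analysis is participants’ actual MMHW registration status".
- **Same section, purpose.** The instrument is used "to measure the effect size that would have been attained without" contamination, which is defined in both directions: "Contamination occurs when women who live in an intervention area do not utilize the MMHW and women who live in a control area utilize" the wallet. The section then says that the resulting effect size "provides a measure of the full effect that the intervention would have induced" had nobody's use departed from assignment.
- **Power calculation.** "We assumed that 50% of participants living in catchment areas of health facilities that received the intervention would adopt the MMHW". No registration figure is given for control areas.
- **Discussion (limitations).** Boundary areas may expose control-area women to the intervention, and the same analysis is offered as the adjustment for this.

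The article does not restrict the result to a subgroup of women. It does not say that the effect is assumed equal in women who register and women who do not.

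**The concern.** Removing contamination in both of the directions defined means that every intervention-area woman uses the wallet and no control-area woman does. That is an effect in all women. An instrumental-variable contrast does not deliver it. Women who would not register under either assignment have the same exposure in both arms, so the comparison says nothing about what registration would do for them. The same holds for women who would register under either assignment.

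At stake is the interpretation of one secondary result. With about half the intervention-area women expected not to adopt, the group about which the data are silent is as large as the group they describe. Registration is each woman's choice and also depends on access to mobile money, so the design does not make adopters and non-adopters alike. A reader told that the figure is the effect of the intervention under full use would take an extrapolation for an estimate.

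**Working it through.** **Inputs**

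- Uptake in intervention areas, u1 = 0.50 (Power calculation). That section speaks of adoption, while the instrumental-variable treatment is registration, so 50% is the nearest stated figure and not an exact match.
- Uptake in control areas, u0: not given. Assumed here to be 0, with 5%, 10% and 20% as a range.
- Intention-to-treat difference in facility-based delivery: 4 percentage points (Power calculation). This is the stated detectable difference, not an expected effect. It serves only as a scale.

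**The plan's own figure.** With 67% against 71%, two-sided 5% and 80% power, the sample size without clustering or loss is 2098 per group, and 2300 per group gives 83.5% power. With the stated intra-cluster correlation of 0.05 and about 30 clusters per arm, power for 4 points is only 25% to 28%. The 4 points is therefore not reproduced under the plan's clustering assumption. That is a separate matter. The argument here holds at any effect size.

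**What the estimate identifies.** Assume that assignment affects outcomes only through registration (exclusion restriction) and that no woman does the opposite of her assignment (monotonicity). There are then three kinds of women:

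- compliers, share c = u1 − u0, mean effect Dc;
- women who never register, share 1 − u1, mean effect Dn if they did;
- women who always register, share u0, mean effect Da.

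On the risk-difference scale:

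- Intention-to-treat difference = c × Dc
- Instrumental-variable estimate = (c × Dc) / c = Dc
- Effect under full conformity = c × Dc + (1 − u1) × Dn + u0 × Da

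Dn and Da appear in the third line but not in the second. The two lines agree if Dn and Da both equal Dc.

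**Numbers with u1 = 0.50 and u0 = 0.** The instrumental-variable estimate is 0.04 / 0.50 = 0.08, or 8 points. The full-conformity effect is 0.50 × 8 + 0.50 × Dn:

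| Effect in non-adopters, Dn (points) | Instrumental-variable estimate (points) | Full-conformity effect (points) |
|---|---|---|
| 0 | 8 | 4 |
| 4 | 8 | 6 |
| 8 | 8 | 8 |
| 16 | 8 | 12 |

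A simulation of 4 million women with a valid instrument and these four values of Dn gave estimates of 7.9 to 8.0 points each time, while the full-conformity effect moved from 4 to 12.

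**If control-area women register.** With the difference held at 4 points, the complier share and the estimate become:

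- u0 = 5%: c = 0.45, 0.04 / 0.45 = 8.9 points
- u0 = 10%: c = 0.40, 0.04 / 0.40 = 10.0 points
- u0 = 20%: c = 0.30, 0.04 / 0.30 = 13.3 points

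Each applies to a smaller group of women.

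**The case against.** The strongest reply is that this is wording in a secondary analysis. The section gives the role of measuring real-life policy impact to the intention-to-treat estimate. No primary estimate, test or sample size depends on the sentence. Contamination adjustment is a cited method, and contamination is defined where it is used. Formal instrumental-variable assumptions and tables of complier characteristics are commonly left to an analysis plan. All of this stands, and it limits the weight of the point. It does not remove it, because the sentence positively states what the estimate measures, and that statement is wrong unless an unstated assumption holds.

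Four stronger readings are tempting, and the documents do not support them.

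- *The estimate overstates the full-use effect.* The direction is unknown. The Madagascar section reports high perceived usefulness in preparatory work, particularly among low-income households, so women who do not adopt could gain more than those who do.
- *Identity checks decide who registers.* The section on cash transfers and vouchers says that "before being eligible to receive restricted cash transfers or electronic vouchers, the account is validated", and it places this step after a new user has registered. The check governs access to benefits, not registration status, which is the treatment variable.
- *The ministry would base national integration on this figure.* The Discussion refers to the trial's results in general and does not single out this analysis.
- *The error could exceed threefold.* That needs about 30% uptake with the difference held at 4 points. The protocol states no such uptake.

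**Conclusion.** The point holds as a correction to what one secondary analysis is said to measure. Under the exclusion restriction and monotonicity, the estimate is the average effect in women whose registration follows assignment: at most about 50% of women on the protocol's adoption assumption, and fewer with any control-area registration. Calling it the effect under full conformity needs equal average effects in compliers and other women, which the article does not state and the trial's data cannot show.

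In the illustration, an estimate of 8 points is compatible with a full-conformity effect of 4, 8 or 12 points, so it could be twice the true value or two thirds of it. Those figures rest on the 4-point scale, zero control registration and assumed effects in non-adopters. They are not bounds.

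The exclusion restriction is itself open to question, because the staff training and equipment given to intervention facilities (Intervention package; Health facility-based procedures) may benefit unregistered women. That issue is separate, but it means that the complier interpretation must be stated with its assumptions.

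**What to change.** 1. Replace the sentence on the secondary analysis with: *estimates, under the exclusion restriction and monotonicity, the average effect among women who register because their catchment was assigned the intervention*. Drop the full-effect wording.
2. Report the estimated share of compliers (registration in intervention areas minus registration in control areas) next to the estimate, using the household survey and dashboard data already planned.
3. Present any effect for all women only as a sensitivity analysis over stated assumptions about the effect in non-compliers. Include no effect, an equal effect and effects larger than the compliers'. A range from zero to equal would not be a bound.

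The cost is one sentence, one reported proportion and, if an all-women figure is wanted, a short table. No new data are needed, and the primary intention-to-treat analysis does not change.
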